## Abstract

**Background:**

By providing information on the relative merits and potential harms of the options available and a framework to clarify preferences, decision aids can improve knowledge and realistic expectations and decrease decisional conflict in individuals facing decisions between alternative forms of action. Decision-making about prenatal testing for fetal abnormalities is often confusing and difficult for women and the effectiveness of decision aids in this field has not been established. This study aims to test whether a decision aid for prenatal testing of fetal abnormalities, when compared to a pamphlet, improves women's informed decision-making and decreases decisional conflict.

**Methods/design:**

A cluster designed randomised controlled trial is being conducted in Victoria, Australia. Fifty General Practitioners (GPs) have been randomised to one of two arms: providing women with either a decision aid or a pamphlet. The two primary outcomes will be measured by comparing the difference in percentages of women identified as making an informed choice and the difference in mean decisional conflict scores between the two groups. Data will be collected from women using questionnaires at 14 weeks and 24 weeks gestation.

The sample size of 159 women in both arms of the trial has been calculated to detect a difference of 18% (50 to 68%) in informed choice between the two groups. The required numbers have been adjusted to accommodate the cluster design, miscarriage and participant lost – to – follow up.

Baseline characteristics of women will be summarised for both arms of the trial. Similarly, characteristics of GPs will be compared between arms.

Differences in the primary outcomes will be analysed using 'intention-to-treat' principles. Appropriate regression techniques will adjust for the effects of clustering and include covariates to adjust for the stratifying variable and major potential confounding factors.

**Discussion:**

The findings from this trial will make a significant contribution to improving women's experience of prenatal testing and will have application to a variety of maternity care settings. The evaluation of a tailored decision aid will also have implications for pregnancy care providers by identifying whether or not such a resource will support their role in providing prenatal testing information.

## Background

Peak obstetric bodies [1-3] recommend that all pregnant women, regardless of age, are provided with information on prenatal screening tests for fetal abnormality. Women often find this information difficult to understand and studies have demonstrated low levels of knowledge [4-7]. Health professionals are an important source of information for women, yet studies have demonstrated they too can also experience difficulty in understanding the inherent complexities related to screening tests [8-10]. Not surprisingly, studies have consistently demonstrated a need to improve women's capacity to make an informed decision regarding prenatal screening tests and the need for women to have a more active role in decision-making. At a minimum, women need to understand the condition(s) for which the testing is being offered, the characteristics of the test and the implications of testing [11].

Decision aids are resources that are designed to assist individuals to make specific and deliberate choices from available options by providing information on the options and outcomes relevant to the individual's health status [12]. They have been found to improve individuals' decision-making and outcomes in a variety of health related areas [13] and have been established as effective in: improving knowledge and realistic expectations of benefits and risks of options, increasing participation in decision-making and reducing decisional conflict without affecting levels of anxiety or satisfaction. Despite promising results among women of advanced maternal age using a decision aid for prenatal diagnostic testing [14], the role of decision aids for women of all ages considering prenatal screening tests has not been established.

We are undertaking a cluster randomised controlled trial to test whether a decision aid for prenatal testing of fetal abnormalities, when compared to a pamphlet, improves women's informed decision-making [11] and decreases their decisional conflict [15]. The trial, called ADEPT (A DEcision Aid for Prenatal Testing of fetal abnormalities), is being conducted in the primary health care setting, as GPs are often the first health professional a woman consults early in pregnancy. Consequently, this setting allows for provision of the allocated information at a gestation when women have the best chance to consider first and second trimester testing options.

## Methods/design

### Design of the intervention

The decision aid for prenatal testing of fetal abnormalities has been developed using the three steps of the Ottawa Decision Support framework: identifying needs, providing decision support and evaluating decision support [16].

The need for a decision aid was identified following a literature search and by conducting focus groups with the target groups relevant to the study: five focus groups with women and four with GPs were conducted in metropolitan and regional Victoria, Australia. The key finding from the GP focus groups was the difficulty GPs experienced in making screening test information appropriate, relevant and understandable to the individual women. In particular, explaining epidemiological concepts was identified as challenging. GPs experienced significant time pressures in the first consultation in pregnancy and strongly supported the development of a tailored resource. The women's focus groups revealed low level of prenatal screening knowledge and diversity in the amount of information women wanted. To accommodate this a flexible paper-based format was drafted, incorporating the use of summary tables and dot points, as well as more detailed information and a resource list. Consistently women identified difficulty with statistical and numeric expressions and this influenced the use of graphs and diagrams throughout the decision aid. Draft formats of the decision aid were piloted with women who were attending a tertiary prenatal clinic in early pregnancy.

The resultant decision aid is a 24-page information booklet and a risk report. The booklet contains information on why testing is offered, the range of chromosomal and physical abnormalities for which tests may be offered, the different types of tests available and the possible outcomes of testing. Also, within the booklet are scenarios of women's decision-making about testing, a list of other resources available and a worksheet to assist women in weighing up the benefits and risks of different options. A risk report sheet detailing an individualised risk estimation for having a pregnancy affected by Down syndrome is generated, based on an algorithm involving the woman's age and gestation [17,18]. The individual risk estimate given to women was obtained through use of a paper-based chart or a CD-ROM, and the GPs were given a choice as to which report generation process suited them best.

The decision aid is being compared to a pamphlet developed by Genetic Health Services Victoria (GHSV). The pamphlet is currently available free of charge within Victoria. It is in the form of a fold out A3 paper size and contains information on maternal age related risk, screening and diagnostic tests, a table summarising the tests available and what conditions they detect.

### Ethics

Royal Australian College of General Practitioners has granted ethics approval to conduct this trial (NREEC 03–16). The trial complies with the principles of the Helsinki Declaration [19]. A plain language statement is provided to all women (see Additional file 1) and GPs in the study and a signed consent form is obtained from all participants at the time of recruitment.

### Setting for the trial

The ADEPT study is being conducted in the primary health care setting of Victoria, one of the south-eastern states of Australia, where approximately 62,000 women give birth each year [20]. All women in Victoria booked to give birth at a publicly funded maternity setting have access to a second trimester maternal serum screening test, free of charge. Within this public system, women identified as being at 'increased risk' for fetal abnormality on the basis of their age (37 years or older) or screening test result, have access to diagnostic testing that is fully funded. Outside these criteria women incur out-of-pocket expenses for most other screening or diagnostic tests, although some costs are covered by a federally funded rebate. All serum samples are sent to a centralised laboratory at GHSV for testing.

In Victoria, the provision of information on prenatal testing options is not uniform. Some women receive information that is verbal and/or written, while others receive no information at all. The pamphlet produced by the GHSV is one of a vast array of written information used throughout the state. While the exact rate of uptake of screening tests in the state is not known, it is estimated that approximately 60% of pregnant women have some form of screening test [21] and utilisation is increasing. An abnormal screening test result was the indication for 44% of diagnostic tests in 2004, compared to 41% for maternal age alone [22].

### Cluster design

Cluster randomisation has been chosen to avoid contamination of the intervention to the control group, which would dilute the difference between the groups thus reducing the power of the study. It has been proposed that the use of cluster randomisation can be justified when the risk of contamination between groups is estimated to be greater than 30% [23]. This level of contamination could reasonably occur in the ADEPT study at the level of the GP, or by women in the intervention group sharing the decision aid with women in the control group within a variety of maternity care environments, as well as through social settings. It is also possible that the paper-based decision aid could be copied and circulated to women in the control arm of the trial.

GPs were randomised either to the intervention arm, providing women with the decision aid, or in the control arm, providing women with the GHSV pamphlet. The individual GP was used as the unit of randomisation. It was envisaged that the cluster design would have the added advantage of assisting participating GPs to adhere to the trial protocol [24], as they would be providing the same resource to all women they recruited. Data are currently being collected from questionnaires completed by women.

### Enrolling GPs in the ADEPT study

Geographical areas were purposively targeted to achieve a geographical spread in the location of general practices throughout the metropolitan area. As approximately one-fifth of Victorian births occur in rural areas [28], these areas were also targeted to ensure non-metropolitan representation. Regional or rural areas were identified on the basis of the number of first trimester samples sent to the centralised laboratory at GHSV in 2004.

Individual letters inviting expressions of interest in the study were sent to GPs (see Additional file 2). The contact details of GPs were obtained from professional organisations, public telephone listings and in-house databases of GPs interested in prenatal testing. Other strategies also involved advertising the ADEPT study through professional organisations and medical media.

### Selection of GPs

Eligibility criteria required that the GP estimated that s/he consults with at least 30 women in early pregnancy within a twelve-month period. Participation was limited to one GP per practice to minimise the potential for contamination previously described. In addition, it was hoped that this restriction would also increase the generalisability of the findings, as GPs who practise together are more likely to share other characteristics such as practice style and attitudes. The 50 GPs participating in the study were asked to each recruit ten women to the trial.

### Randomisation of GPs

A person independent to the study has conducted all randomisation procedures for this study. Initially, the names of the 63 GPs expressing interest in the study were randomly sorted. GPs were contacted by phone using the numerical order of the list of names, until verbal consent to be randomised to either arm was obtained from 50 GPs. This addressed the potential for selection bias inherent in cluster trials [23,24,29], where participation rates differ between the groups following allocation.

The GPs were stratified by location (metropolitan/rural) in an attempt to address the association between geographical location and women's uptake of prenatal diagnostic testing [30]. Random allocation was obtained using a computer generated random list of numbers.

### Enrolling women in the ADEPT study

Each GP was asked to provide information on the ADEPT study and to offer participation to all pregnant women meeting the study's selection criteria (see Additional file 3). The risk of selection bias recognised in cluster trials [31] will be measured by way of an audit (see Additional file 4) using details collected by the GP on the age, parity and country of birth of all women meeting the selection criteria during the recruitment period. Australian GPs are primarily funded by a fee for service system and receive no funding (personal or infrastructure) for involvement in research. GPs have been reimbursed for the time spent enrolling a woman to the study ($30AUD/woman).

GPs needed to obtain written informed consent from women wanting to participate in ADEPT as well as the woman's contact details and estimated date of delivery. These details were faxed/posted to the project office. The GP provided each participating women with an information resource (decision aid or pamphlet) and the first questionnaire, as well as written instructions, an information sheet and a copy of the consent form she signed.

### Inclusion criteria for women

Pregnant women attending a participating GP were eligible to participate provided they were aged 18 years or older and were equal to, or less than, 12 weeks gestation.

### Exclusion criteria for women

Women were excluded if they were non-English speaking, were unable to give written informed consent or required genetic counselling due to a family history of an inherited condition or recurrent risk for fetal abnormality. Exclusion criteria also included having already undertaken testing for fetal abnormality in this pregnancy, experiencing vaginal bleeding or currently having a known multiple pregnancy.

### Data collection from women

Women were asked to complete two questionnaires, the first by 14 weeks gestation and the second at approximately 24 weeks gestation. The initial questionnaire was given to the woman by her GP and the second questionnaire was forwarded to her postal address by the project team. Stamped addressed envelopes have been provided for the return of both questionnaires.

Once written informed consent was obtained from the woman by her GP, an enrolment form detailing the date, woman's name, contact details and estimated due date was faxed to the study office. This information was entered into a database to manage the reminder system for the questionnaires as well as the mail-out of the second questionnaire.

Using a modification of the technique described by Dillman [32], a two-stage reminder system is in place to maximise the response rate of the questionnaires. Women are contacted with a reminder letter two weeks after the questionnaire is due if it has not been received. A phone call reminder follows in a further two weeks if the questionnaire remains unreturned.

### Blinding

Blinding of researchers was not practical in this study, however a person independent of the study has kept the master list of all randomised groups and will audit the integrity of the randomisation prior to analysis.

Participating women were made aware that two methods of providing information were being trialed but were not advised of the alternative resource to the one they received.

### Allocation concealment

Concealment of allocation was achieved by obtaining GP's verbal consent to be randomised prior to the conduct of the randomisation. The research team members were not advised of the allocation until consent had been obtained from all GPs. GPs were unaware of the arm of the trial to which they had been randomised until the time of the practice visit.

### Data entry quality control

Prior to analysis, a random sample of ten percent of the data entry will be audited. A person independent of the study will conduct the sampling and audit. The rate of accuracy will be reported.

### Scales

ADEPT is using validated and psychometrically robust self-report scales.

The Multi-dimensional Measure of Informed Choice (MMIC) [11] scale defines an informed choice as one that is based on relevant knowledge, is consistent with a person's values and is behaviourally implemented. Three dimensions are incorporated in this measure: knowledge, attitude and uptake. There are eight knowledge items and four items on attitudes to screening tests. A record of test uptake is included in the measure. Dichotomous outcomes are classified as informed choice or uninformed choice. The classification of an informed choice is determined by a score higher than the midpoint of the knowledge scale (>4), higher than the midpoint of the attitude scale (>12) and having the test. Equally, a choice is classified as informed when a score is higher than the midpoint of the knowledge scale (>4), less than the midpoint of the attitude scale (equal or <12) and not having the test [33].

The Decisional Conflict Scale [15] contains 16 items divided into three sub-scales: uncertainty about selection of alternatives; specific factors contributing to uncertainty and perceived effectiveness of decision-making. Respondents use a five-point Likert scale (1 = strongly agree to 5 = strongly disagree). The mean scores are reported for the total scale and each sub-scale. Higher scores indicate higher decisional conflict.

The Attitudes to the Fetus/Neonate [34] measure consists of 15 adjectives and respondents use a seven point scale (0 = Not at all to 7 = extremely) to describe their feelings in relation to being pregnant (nine items) and towards the fetus (six items). By reversing specific items the mean scores are calculated for attitudes to pregnancy and the fetus, with higher scores indicating a more positive attitude.

The Edinburgh Postnatal Depression Scale [35] has been validated to use prenatally. It contains ten items and respondents have four options available to indicate the frequency of the event based on their experience of the previous week. With the reversing of specific responses, items are scored (1–4) and women can be classified as probably clinically depressed (≥ 13) or not (<13).

The short version of the Speilberger State- Trait Anxiety Inventory (STAI – State) contains six items [36]. Respondents use a four-point Likert scale to indicate how they feel now (1 = Not at all to 4 = Very much). With the reversing of specific responses, mean scores are reported with higher scores indicating greater anxiety.

The Satisfaction with Decision [37] scale contains five items and respondents use a five point Likert scale (1 = strongly agree to 5 = strongly disagree). With the reversing of specific responses, mean scores are calculated with higher scores indicating greater satisfaction.

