### Outcomes

The two primary outcomes for the study are informed choice and decisional conflict. Informed choice will be measured by the percentage of women in each arm of the trial identified as making an informed choice using the MMIC [11]. Decisional conflict will be measured by the difference in mean scores of the Decisional Conflict Scale [15] between women in each arm. Both primary outcomes will be measured based on data from the first questionnaire to reflect women's experience closest to the time they were making decisions about prenatal testing.

Secondary outcomes include attitudes to the pregnancy/fetus, depression, anxiety, and acceptability of the written information by women and GPs. These outcomes will be measured using data from the first questionnaire. Women's satisfaction with their decision [37] will be assessed using data from the second questionnaire.

Changes in primary and secondary outcomes will be measured by comparing responses from the second questionnaire with the first. Attitudes to the pregnancy/fetus will be assessed using the scale developed by Reading et al (1984) [34] by measuring the difference in mean scores between women in both arms of the trial. Depression will be measured using the difference in percentages of women in both arms of the trial identified as being probably clinically depressed on the EPDS [35]. Anxiety will be measured as the difference in the mean Anxiety STAI-State (short version) score of women in both arms of the trial [36]. The acceptability of the decision aid/pamphlet to women and GPs will be measured by comparing the difference in proportions of descriptive items between women in both arms of the trial and comparing content analysis of open-ended comments.

Satisfaction with decision making will be measured using the difference in mean Satisfaction with Decision Scale [37] scores between women in both arms of the trial.

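### The depression scale's item scoring (1–4) and its cut-off (13 or more) do not belong to the same scoring, so the secondary depression outcome is wrong as written

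*Protocol article*

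**What the plan says.** The Scales section of the protocol article introduces its instruments with the statement "ADEPT is using validated and psychometrically robust self-report scales". Of the Edinburgh Postnatal Depression Scale it says "It contains ten items and respondents have four options available to indicate the frequency of the event", and then, after reversal of certain responses, "items are scored (1–4) and women can be classified as probably clinically depressed (≥ 13) or not (<13"). It gives no range for the total, no rescaling and no other coding of the items.

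The Outcomes section lists depression among the secondary outcomes ("Secondary outcomes include attitudes to the pregnancy/fetus, depression, anxiety, and acceptability of the written information by women and GPs"), to be taken from the first questionnaire. It fixes the measure as follows: "Depression will be measured using the difference in percentages of women in both arms of the trial identified as being probably clinically depressed". No comparison of mean depression scores is described. The same section says that changes in primary and secondary outcomes between the two questionnaires will also be measured.

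**The concern.** A threshold for probable clinical depression should separate women with a substantial symptom load from the rest. With every item contributing at least 1 point, a woman with the most favourable answer on all ten items already scores 10. A cut at 13 then leaves almost no room below it.

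The outcome is defined entirely by this classification. If the printed rule were programmed, the reported percentages would describe how many women have any more than trivial symptoms, under a label that says something much stronger. The comparison between arms, and the change from the first to the second questionnaire, would carry the same mislabelling. The data-entry audit described in the article would not reveal it, because items correctly entered as 1–4 would pass and still be misclassified.

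**Working it through.** **Inputs from the protocol article (Scales).** Ten items; four options each; items scored 1 to 4; case if 13 or more. The article states no total-score range, so there is no figure of its own to reproduce.

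**What the cut-off refers to.** An item mean cannot exceed 4, so 13 can only be a cut on the summed total.

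**Range as written.**
- Minimum = 10 × 1 = 10; maximum = 10 × 4 = 40.
- Distance of the cut from the floor = 13 − 10 = 3 points.
- Position in the range = (13 − 10) / (40 − 10) = 3/30 = 10%.
- Example of a woman who just meets it: the least severe answer on seven items and the next on three, 7 × 1 + 3 × 2 = 13.

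**Response patterns below the cut.** A non-case must total 10, 11 or 12, that is 0, 1 or 2 points above the floor.
- 0 points: 1 pattern.
- 1 point: 10 patterns.
- 2 points: 10 patterns with one item raised by two, plus 45 with two items raised by one, 55 in all.
- Sum = 1 + 10 + 55 = 66 of 4^10 = 1,048,576 patterns.

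This count shows where the cut sits. It is not a prevalence, because women do not answer at random.

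**The same cut on a 0–3 coding (an assumption; the article does not state it).**
- Range 0 to 30; 13 lies 13/30 = 43% of the way up.
- Moving from 0–3 to 1–4 adds 1 to each of ten items, so a zero-based 13 equals 13 + 10 = 23 on the 1–4 coding.
- Conversely, 13 on the 1–4 coding equals 13 − 10 = 3 on the zero-based coding.

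**Illustration of size.** The article gives no score distribution. Assume a negative binomial zero-based total with mean m and standard deviation s, so that the size parameter is m² / (s² − m) and the probability parameter is m / s². Compare P(total ≥ 13), the cut on 0–3 coding, with P(total ≥ 3), the cut as printed for 1–4 coding.

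| Assumed mean, SD | Cases if 13 is a cut on 0–30 | Cases under the printed rule |
|---|---|---|
| 6, 4.5 | 8.8% | 76.9% |
| 7, 5 | 13.2% | 82.5% |
| 8, 5 | 16.9% | 89.4% |

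The percentages depend on the assumed mean, spread and shape. The 10-point shift between the two codings does not.

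**The case against.** **It may be only a reporting slip.** The instrument is presented as validated and its source is cited. The printed 1–4 may simply number the four options, much as neighbouring scales in the article are numbered from 1. Harm arises only if the sentence was programmed as it stands, and the article does not show that it was. This stands, and is a reason to check rather than to assume an error in the data. It does not make the sentence right: both numbers are stated, and they conflict.

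**The consequences are limited.** Depression is one of several secondary outcomes. Neither primary outcome (informed choice, decisional conflict) uses the scale, and nor does the sample size. A woman's answer is the same however the options are numbered, so retained item responses can be recoded. This stands too.

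**Stronger readings that the documents do not support.** A reader might infer that the outcome hits a ceiling and cannot show harm or benefit. The illustration speaks against that: when the assumed mean rises from 7 to 8 with SD 5, the printed rule's percentage moves by 89.4 − 82.5 = 6.9 points, against 16.9 − 13.2 = 3.7 points on the zero-based cut. The percentage still responds to a shift in scores; it does not measure what its label says. A reader might also infer that the item range is certainly the error and 13 the right cut. The article contains no 0–3 coding and no total range, so it does not settle which element is wrong. Finally, the statement that most women would be classed as depressed rests on an assumed distribution, not on the article.

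**Conclusion.** The point holds as an inconsistency in a stated classification rule for a secondary outcome. As printed, the cut lies 3 points, or 10% of the range, above the minimum score, and nothing elsewhere in the article corrects it. That much needs no assumption beyond the cut applying to the summed total. Used literally, the rule makes the depression percentage invalid as a measure of probable clinical depression.

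The illustrated size, about 77–89% classified instead of 9–17%, rests on two assumptions outside the article: the negative binomial distribution with the stated means and SDs, and the supposition that 13 was meant for a 0–30 total.

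To call the outcome unusable would go too far. The fault lies in the rule as written and can be repaired at analysis if item responses are kept. The primary outcomes and the sample size are unaffected.

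**What to change.** Before any woman is classified, check the item scoring and the cut-off against the scale's cited source and correct the Scales section so that the two agree. Check that the database coding and the analysis code follow the same rule at both questionnaires.

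If the source confirms 13 as a cut on a 0–30 total, either score the items 0–3 and classify at 13 or more, or keep 1–4 coding and classify at 23 or more. These are arithmetically the same rule. If the source shows something else, follow it and state the total-score range beside the cut-off.

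The cost is one corrected sentence and, if needed, a recode. The article describes data collection as still under way, so this can be done before analysis, with no loss of data and no change to the design.
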